### Hypotheses

The primary hypothesis of the SPIBI is that the quality of the parent-child interaction will improve, and more specifically, that the emotional availability of both the child and parent will be higher in the intervention dyads than in the control dyads post-intervention.

The secondary hypotheses concern the children and the parents, respectively. The secondary hypotheses concerning the children are that the children in the intervention group will have enhanced development compared to the control children during the intervention, with an enduring effect concerning their general development, executive function, motor development, neurological development and autistic symptoms. Additional secondary hypotheses are that when preschool teachers are asked about their view of their extremely preterm pupil, they will describe the children in the intervention group as more participatory and playful than the control children are.

The secondary hypotheses concerning the parents are that compared to parents of children in the control condition, parents of the children in the intervention condition will be less depressed, less anxious and more resilient to stress, as well as describe themselves as having higher parental self-efficacy.

All hypothesises are formulated as objectives with specific outcomes attached to them as well as period of activities in Table 1.

**Table 1 Tab1:** Project framework: specific objectives, outcomes and period of activities

Specific Objectives	Outcomes	Period of activities
Objective 1:		
To improve the quality of the interaction between parents and their extreme preterm children	All participants will be filmed during a free play situation during a 20 min interaction. The video films will be analyzed using the Emotional Availability Scales (EAS).	Parent-child interactions will be video filmed at 12 months corrected age (at the end of the intervention) and again at 2 years corrected age (1 year post-intervention).
Objective 2:		

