### Sample size and statistical power

The hospitals in Stockholm treat more than 100 extremely preterm infants every year, but several of them are not residents of Stockholm County, which is a prerequisite for study inclusion. The study team is prepared to recruit 130 participants, 50% of which will be randomized to the SPIBI intervention. The sample size is based on feasibility, and the assumption is that the effect size of the intervention on the primary outcome measure Emotional Availability Scales (EAS) will be moderate, i.e., Cohen’s d = 0.5. This is largely in line with the results of Flierman et al. [50] for the sensitivity scale of the EAS in the previously mentioned Dutch trial. Hence, we aim to recruit 130 participants, which gives us a power of 0.8 given a normal distribution and an alpha value of 0.05.

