### Outcome measurements

Since the SPIBI is a multi-professional intervention, the outcome is measured across several domains: outcomes concerning emotional availability in the dyadic relation, outcomes measuring child development and outcomes related to parental mental health and parenthood.

The *primary outcome* is the Emotional Availability Scales (EAS) [65], which will be used primarily at 12 months corrected age but then again at 24 months corrected age. The primary coder is blind to group allocation, whereas the second coder, who is used for interrater reliability checks in 20% of the cases, is not. The scale has four parental dimensions (sensitivity, structure, non-intrusiveness, and non-hostility) and two child dimensions (child responsiveness and child involvement). Each subscale has a maximum score of 29 and a direct score of 1–7. It is hypothesized that higher scores will be observed in the intervention group. Previous international studies have shown significant effects of parental sensitivity and structuring as well as child involvement [50], which also seem to be the subscales most indicative of maternal anxiety in the NICU [66].

The *secondary outcome measurements* are listed below. For measuring the cognitive, language, and motor development of the children, the Bayley Scales of Infant and Toddler Development, Third Edition (BSID-III) [67], will be used at 24 months corrected age. Composite scores are standardized to mean (SD) scores of 100 [15], based on age-matched normative data. The secondary hypothesis is that the mean will be higher in the intervention group.

The child’s executive function at 24 and 36 months corrected age will be measured with the Behaviour Rating of Executive Function, Parental Version (BRIEF-P) [68, 69]. All 5 subscales (*inhibit, shift, emotional control, working memory and plan/organize)* will be used, and the hypothesis is that the intervention group will have fewer executive problems reported.

Child’s motor development will be measured by the Alberta Infant Motor Scale (AIMS) [70, 71] at 3 and 12 months corrected age. The range of the AIMS is 0–58 points, with a hypothesis of higher scores for the intervention group.

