### Statistical analysis plan

Data will be analysed using intention to treat analysis for the primary outcome and separate testing with multiplicity adjustments for secondary outcomes. Data will be analysed using SPSS version 25 (IBM, New York) and reported according to the CONSORT statement for RCTs. Descriptive parametric statistics will be presented as percentage for categorical variables and as mean and SD for continuous variables such as age or centiles if the data is skewed. Comparisons between the two groups will be performed with Mann-Whitney U test for independent samples. Subgroups with additional analyses will also be used for detaching outcome differences according to number of home-visits in total, additional medical diagnoses and whether one or two parents participated in the intervention. The level of significance is specified at 0.05. To account for repeated measures, to model within-subject variance, and to handle correlated data of continuous variables a linear mixed model will be used. An interaction term will be introduced in the model to examine heterogeneity effect. For binary and ordinal outcome variables Generalized Estimating Equation (GEE) will be employed. For the main analysis no missing data will be imputed. However, classical multiple imputation methods will be used for an additional sensitivity analysis if any of the included variables has more than 5% missing observations. The GEE is a technique which produces unbiased estimates under the assumption that missing observations will be missing at random. An amended approach of weighted GEE will be employed if missingness is found not to be at random. We will perform residual analysis to assess model assumptions and goodness-of-fit.

Generalized linear modelling will be used for outcome variables that are not repeated to create regression models with distribution of the binary and ordinal dependent variables.

The Bonferroni method will be used to appropriately adjust the overall level of significance for multiple comparisons. Count variables will be analyzed using the Poisson regression model. Qualitative variables from the semi-structured interviews will be analysed for their thematic content. The Pearson chi-square test will be used to detect associations between categorical variables, and the mean and standard deviation will be presented for normally distributed continuous variables.

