Intervention (s)	Active comparator: Home-based post-discharge intervention for extremely premature infants and their parents. The intervention consists of one hospital visit, nine home-visits and two telephone calls during the first year corrected age, specifically from 1 week before discharge to 12 months corrected age. The intervention is strengths-based working with the infant-parent interaction, supporting infant development and strengthening the parent in his/her role.		
	Control condition: The participants of the Control Group receives treatment as usual, which consists of a regular follow-up program with neurodevelopmental assessment at term age, 3 months corrected age, 12 months corrected age, 24 months corrected age and 66 months corrected age. Compared to children not participating in the study, the control group will receive an extended follow-up program, with assessment and questionnaires at term age, 3 months corrected age, 12 months corrected age, 24 months corrected age and 36 months corrected age. Participants in the control group will be referred to specialized care when needed.		
Key Inclusion and Exclusion Criteria	Inclusion Criteria: • extremely premature born infants • close to discharge from their neonatal intensive care unit hospital stay at Stockholm county council (Stockholms Läns Landsting).		
	Exclusion Criteria: • Children with parent/parents who do not communicate in Swedish or English. • Patients not residing in Stockholm County. • Acute surgery patients who will spend a lot of time at hospitals far from Stockholm		
Study Type	Interventional		
	Study design Method; randomized Masking; Semi-masked, primary outcome assessor is blind to allocation Assignment; Parallel Purpose; The purpose of the SPIBI is to improve parent-child interaction, child development and parental mental health		
	Phase; Not fully applicable, Phase II/Phase III		
Date of First Enrollment	September 2018		
Sample Size	Planned: 130		
	Today (22nd of November 2019): 48		
Recruitment Status	Recruiting		
Primary Outcome (s)	Emotional Availability of parent and child measured with Emotional Availability Scales EAS.		
	Time point: 12 months corrected age		
	Method: Video Observation of 20 min parent-child interaction, assessed with the manualized method of EAS consisting of 4 parent-specific domains and 2 child-specific domains.		

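### The primary outcome is the six-dimension EAS with no lead variable, composite or success rule, while the stated alpha 0.05 and power 0.8 describe a single test

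*Protocol article*

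**What the plan says.** Under Outcome measurements, the primary outcome is the EAS, "which will be used primarily at 12 months corrected age but then again at 24 months corrected age". The scale is then described: "The scale has four parental dimensions (sensitivity, structure, non-intrusiveness, and non-hostility) and two child dimensions (child responsiveness and child involvement"). On scoring: "Each subscale has a maximum score of 29 and a direct score of 1–7". No dimension is singled out as primary. The registration summary table near the end of the article does the same; the outcome is "assessed with the manualized method of EAS consisting of 4 parent-specific domains and 2 child-specific domains".

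Under Hypotheses, the primary claim is that "the emotional availability of both the child and parent will be higher in the intervention dyads than in the control dyads post-intervention".

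Under Sample size and statistical power, the number of participants is said to rest on feasibility, with the assumption that the effect on the EAS "will be moderate, i.e., Cohen’s d = 0.5". This is described as broadly agreeing with an earlier result "for the sensitivity scale of the EAS in the previously mentioned Dutch trial". The section concludes that 130 participants give power 0.8 at alpha 0.05.

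The Statistical analysis plan section opens with: "Data will be analysed using intention to treat analysis for the primary outcome and separate testing with multiplicity adjustments for secondary outcomes". Further on, it says Bonferroni will be used for multiple comparisons, without naming the family or the number of tests. The significance level is 0.05.

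**The concern.** A single alpha and a single power figure need a single test, or a stated rule for combining several. Here the primary outcome is an instrument with six dimensions, and several readings of success remain open: one dimension, any dimension, one parent and one child dimension, or all six. These readings differ in both type I error and power.

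The opening sentence of the analysis section separates the primary outcome from the outcomes that receive multiplicity adjustment. Followed as written, each EAS dimension could be tested at 0.05 and any significant one reported as the primary result. The general Bonferroni sentence might close that gap, but whether it does cannot be read from the text. What is at stake is the credibility of the primary claim, which the Discussion links to possible introduction of the programme at national or cross-national level.

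**Working it through.** **Inputs.** From the article: N = 130, half per arm (65); d = 0.5; alpha 0.05; power 0.8; six EAS dimensions (four parent, two child). Assumed, because the article does not give them: two-sided testing, no dropout, and a common correlation ρ between the test statistics of the dimensions.

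**1. The plan's own figure.** Noncentrality = d × √(n/2) = 0.5 × √32.5 = 2.85. Normal approximation: Φ(2.85 − 1.96) = Φ(0.89) = 0.813. Noncentral t: 0.808. The stated 0.8 is reproduced for one two-sided test. One-sided power would be 0.883, which does not match.

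**2. Any of six at an unadjusted 0.05.** If independent: 1 − 0.95⁶ = 1 − 0.735 = 0.265. With positive correlation, simulate z_j = √ρ·g + √(1−ρ)·e_j under no effect and count the runs in which any |z_j| > 1.96 (table below).

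**3. Conjunctive rules.** Add 2.85 to each z_j and require z_j > 1.96 for two scales (one parent, one child) or for all six. The error rate stays within 0.05, but power falls.

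| Assumed ρ | False-positive chance, any of six at 0.05 | Power, one parent and one child scale | Power, all six |
|---|---|---|---|
| 0 | 0.27 | 0.66 | 0.29 |
| 0.3 | 0.24 | 0.69 | 0.42 |
| 0.5 | 0.21 | 0.71 | 0.50 |
| 0.7 | 0.16 | 0.73 | 0.59 |
| 0.9 | 0.11 | 0.77 | 0.69 |

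The power columns assume d = 0.5 on every dimension involved.

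**4. Bonferroni over six.** Alpha per dimension = 0.05/6 = 0.0083. Power for one named dimension is 0.57 (noncentral t; 0.58 by the normal approximation). Total N for 80% power on that dimension would be 198 (t).

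The chance that at least one dimension passes is a different quantity. It depends on how many dimensions have d = 0.5 (simulated with critical value 2.638):

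| Assumed ρ | One responds | Three respond | All six respond |
|---|---|---|---|
| 0.3 | 0.59 | 0.87 | 0.96 |
| 0.5 | 0.58 | 0.82 | 0.91 |
| 0.7 | 0.58 | 0.77 | 0.84 |
| 0.9 | 0.58 | 0.69 | 0.74 |

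Family-wise error under this rule stays below 0.05: 0.046, 0.041, 0.033 and 0.021 at the four correlations.

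**The case against.** The strongest counter-argument is that the general Bonferroni sentence is unrestricted and may cover the EAS dimensions. It would be wrong to infer that adjustment is confined to secondary outcomes. If the sentence applies and any of six counts as success, alpha is held and power can reach 0.8 or more. A reader might conclude that adjustment necessarily destroys the power; the second table shows that it does not. What remains is that the text neither includes the EAS in the Bonferroni family nor states the any-of-six rule, and that the favourable power depends on several dimensions responding and on correlation that is not high.

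Three other inferences go further than the document allows:

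- That d = 0.5 was derived from the sensitivity scale. The article gives feasibility as the basis for the sample size and cites the sensitivity result as support. Sensitivity is therefore a natural candidate for the primary variable, but not one the article has already chosen.
- That there are twelve primary tests because each dimension has two scores. Nothing says both scores will be tested. The score type simply needs to be named.
- That the EAS has no total. The article is silent. It does state an overall score for the Ages and Stages Questionnaire and none for the EAS, but silence does not show that none exists.

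It can also be said that such detail belongs in a separate analysis plan. That holds for model details. The primary variable and what counts as success are protocol matters, and the article attaches a one-test power claim to a multi-dimension outcome in its own text.

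**Conclusion.** The point stands in this form: the primary EAS variable and success rule are not fixed, and the scope of the Bonferroni adjustment is undefined, so the stated alpha and power cannot be tied to a particular test. The sample-size arithmetic itself is right for one test.

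The consequence depends on the reading. Any of six unadjusted gives a false-positive chance of about two to five times the nominal 0.05 (0.11 to 0.27). Requiring both a parent and a child scale, the reading closest to the hypothesis, gives power 0.69 to 0.77 at correlations of 0.3 to 0.9; requiring all six gives 0.42 to 0.69. Bonferroni over six with any-of-six success holds alpha, and power ranges from about 0.58 to 0.96.

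All correlated figures rest on an assumed equal correlation between dimensions, and the power figures on d = 0.5 wherever an effect is present. The independent-test value of 0.27 is the top of the error range, because positive correlation lowers it. This should be settled before unblinding, since otherwise the choice of dimension could follow the data.

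**What to change.** Choose one of two routes and write it into the protocol and analysis plan before unblinding.

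**Single primary.** Name one EAS variable (a dimension or a defined composite, with its score type) at 12 months corrected age, tested at two-sided 0.05. This keeps N = 130 and power 0.81. Parental sensitivity is a natural option because it is the scale cited in support of d = 0.5. Test the remaining dimensions afterwards in a fixed sequence or by Holm, with a child scale first, and reword the primary hypothesis to match.

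**Primary family.** State that the EAS dimensions, or one parent and one child scale as co-primaries, form the primary family. Give the success rule and the adjustment, say whether the Bonferroni sentence applies to this family, and restate the power for that rule.

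Either route costs only wording at this stage. With a single primary, a positive result on another scale alone can no longer be called the primary result. If that primary is a parent scale, the child half of the hypothesis becomes a later step, which is a real change to the stated aim. With a family, the hypothesis is preserved, but the power to be reported is less favourable than 0.8 under most rules.

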Parental depression will be measured by Hospital Anxiety and Depression Scale (HADS) [72, 73] at term age and at 12, 24 and 36 months corrected age. On the HADS, the range for the depression subscales is 0–21, and the range for the anxiety subscales is 0–21. It is hypothesized that lower scores will be observed for the parents of the children in the intervention group.

Parental anxiety will be measured by the State-Trait Anxiety Inventory (STAI) [74] at term age and at 12, 24 and 36 months corrected age. Both the state and trait scales have a maximum score of 80 points. It is hypothesized that lower scores will be observed for the parents of the children in the intervention group.

Parental self-efficacy will be measured by the Parental Self-Efficacy Scale (PSE) [75] at term age and at 12, 24 and 36 months corrected age. The PSE has 24 items for children at term age and at 12 and 24 months corrected age, while it has 48 items for children of older ages. All items are rated on a 0–10 scale. It is hypothesized that higher scores will be observed for the intervention group at 12, 24 and 36 months corrected age.

Parental resilience will be measured by the Resilience Scale (RES) [76, 77] at term age and at 12, 24 and 36 months corrected age. The RES is a 25-item scale with a 7-point Likert scale. It is hypothesized that higher scores will be observed in the intervention group.

The *other outcome measurements* are listed below. The Hammersmith Neonatal Neurological Outcome (HNNE) is used at term age as a baseline measurement. Post discharge neurological development will be assessed with the Hammersmith Infant Neurological Examination (HINE) [78–80] at 3 months, 12 months, and 24 months corrected age. It is hypothesized that higher scores will be observed for the intervention group. The HINE can be used for infants 2–24 months of age and has optimal scores as well as cut-off values for future less fortunate motor outcomes. It includes 26 items assessing posture, movements, muscle tone, cranial nerve reflexes and reactions, with a score range of 0–3 for each time, thus yielding a possible sum of 0–78 points.

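### AIMS and PDMS are described as raw scores at nominal ages, and the named rank test cannot use the child's exact age on the assessment day, so a little precision is lost

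*Protocol article*

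**What the plan says.** Under *Outcome measurements*, AIMS is taken "at 3 and 12 months corrected age", and the article says: "The range of the AIMS is 0–58 points, with a hypothesis of higher scores for the intervention group". No centile or age-normed score is mentioned for it. PDMS is taken once, at 12 months corrected age, and is described by five raw subscale ranges, from 0–30 (object manipulation) to 0–138 (locomotion). The same section handles BSID-III differently: its composite scores are standardised, "based on age-matched normative data".

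The *Statistical analysis plan* section states: "Comparisons between the two groups will be performed with Mann-Whitney U test for independent samples". It also assigns repeated continuous data to a linear mixed model. For outcomes that are not repeated it mentions generalised linear modelling, but for binary and ordinal dependent variables. It names no covariate and does not say how time is coded in the mixed model.

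The registration table lists AIMS among the key secondary outcomes. PDMS belongs to the other outcomes.

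**The concern.** Raw infant motor scores can be expected to rise with age. Corrected age allows for prematurity, but not for children being seen some days or weeks either side of the nominal visit. If a raw score is compared by nominal visit alone, part of the between-child spread is only spread in age on the day. BSID-III removes this through its norms. AIMS and PDMS, as described, do not, and a Mann-Whitney test has no place for an age covariate.

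For PDMS this is the only group comparison that the article names, if the subscales are treated as continuous. It is a single-visit outcome, so the repeated-measures model does not reach it. At stake is some avoidable noise in one key secondary outcome and one other outcome.

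**Working it through.** **The plan's own figure.** The article gives power for the primary outcome only: "we aim to recruit 130 participants, which gives us a power of 0.8 given a normal distribution and an alpha value of 0.05", with the effect on the "Emotional Availability Scales (EAS) will be moderate, i.e., Cohen’s d = 0.5", and with allocation "50% of which will be randomized to the SPIBI intervention", so 65 per arm. Two-sided testing is assumed. Normal approximation: 0.5 × √(65/2) = 2.850; 2.850 − 1.960 = 0.890; power 0.813. The t-test gives 0.808. A Mann-Whitney test with efficiency 0.955 gives about 0.79 to 0.80. The stated 0.8 reproduces. It concerns EAS and does not depend on this point. It serves below only as a reference design.

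**Inputs that the article does not give (assumptions).**
- AIMS gain per month: 3 to 4 points as the working range, with 1 to 6.4 as the outer range. A 0–58 scale used from 3 to 12 months cannot show a mean gain above 58/9 = 6.4 points per month.
- SD at a fixed age: 6.5 as the working value, 5 to 10 as the range.
- Effect: 0.5 SD at a fixed age, borrowed from the primary outcome.
- Assessment window: uniform over ±3 weeks. This is borrowed from the home-visit schedule in the section on programme content. No assessment window is given.

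**Formula.** Leaving age out multiplies the variance by 1 + (slope × SD of age / SD of score)². With ±3 weeks, the SD of age is 3/√3 = 1.73 weeks = 1.73/4.35 = 0.398 month. The effective effect size is 0.5 divided by the square root of the inflation.

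| Gain per month | SD | Window | Variance inflation | Power without age | Power with age |
|---|---|---|---|---|---|
| 1 | 10 | ±3 wk | 0.2% | 0.813 | 0.813 |
| 2 | 6.5 | ±3 wk | (2 × 0.398/6.5)² = 1.5% | 0.808 | 0.813 |
| 3 | 6.5 | ±3 wk | (3 × 0.398/6.5)² = 3.4% | 0.801 | 0.813 |
| 4 | 6.5 | ±3 wk | (4 × 0.398/6.5)² = 6.0% | 0.791 | 0.813 |
| 4 | 5 | ±3 wk | 10% | 0.775 | 0.813 |
| 6.4 | 5 | ±3 wk | 26% | 0.719 | 0.813 |
| 3 | 6.5 | ±6 wk | 13.5% | 0.763 | 0.813 |
| 4 | 6.5 | ±6 wk | 24% | 0.726 | 0.813 |

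At ±6 weeks the SD of age doubles to 0.797 month. That window has no source in the article and only shows the direction.

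**Separating age from the rank test.** In simulation (gain 3 and 4, SD 6.5, ±3 weeks), Mann-Whitney power is 0.775 and 0.765, against 0.801 and 0.808 for a linear model with exact age. The gaps are 2.6 and 4.3 points. With no age spread at all, Mann-Whitney has 0.791 and the t-test 0.809, so 1.8 points of each gap belong to the rank test itself. The remainder, 0.8 and 2.5 points, is the age component and agrees with the table.

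**Chance imbalance in age.** With ±3 weeks, the difference in mean assessment age between arms has an SD of 1.73 × √(2/65) = 0.30 week. This is ordinary sampling error, and the test already allows for it.

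**PDMS.** The same formula applies and depends only on the ratio of monthly gain to SD. The article gives neither, so no separate figure is offered.

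**The case against.** The strongest reply is that this rests on silence. A condensed article commonly leaves covariates, time coding and score conversion to the full plan, and a raw range only describes the instrument. That stands in part. For AIMS, which is repeated, the article also names a mixed model, and nothing prevents that model from carrying exact age. It does not dispose of the point, because the article does fix a two-group test that cannot take a covariate, and for PDMS it names no other continuous-outcome comparison.

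A reader might infer more than the documents support:
- **That unequal visit timing will pass for a treatment effect.** This needs a systematic difference in assessment age between arms. A 1-week difference at 4 points per month and SD 6.5 would give 4 × 0.23/6.5 = 0.14 SD and about 13% rejections with no effect. The article suggests no such difference: the *Control group* section gives both arms the same assessment ages. Contact with the study team does differ by arm, but no effect of that on assessment dates is stated.
- **That HINE and ASQ share the problem.** No growth rates are given. HINE keeps one range, "thus yielding a possible sum of 0–78 points", over 2–24 months, and ASQ has the same 0–300 range at 12, 24 and 36 months. Both are also repeated, so the mixed model is named for them too.
- **That exact age should replace the visit as the time axis.** In its simplest linear form this would force one straight line from 3 to 12 months and blur the visit-specific contrasts.

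**Conclusion.** The point holds as a small precision gain for AIMS and PDMS. It does not hold as a claim of bias or as one about all raw-scored outcomes. On the working assumptions (3 to 4 AIMS points per month, SD 6.5, ±3 weeks, 65 per arm, effect 0.5 SD), unadjusted age costs about 3 to 6% of variance and 1 to 2 power points. Over the wider range at ±3 weeks, the loss runs from nothing to about 9 power points at the most extreme slope and smallest SD. All of these inputs are assumed, so the direction is firm and the size is not. The primary outcome and its stated power are untouched. This is a worthwhile refinement of minor importance.

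**What to change.** For PDMS, base the group comparison on a linear model. For AIMS, base it on the linear mixed model already planned. In both, add exact corrected age at assessment as a covariate, centred within visit over both arms together (centring within arm would undo the adjustment). For AIMS, keep nominal visit as the time factor so that the 3- and 12-month contrasts remain. Keep the Mann-Whitney test as a sensitivity analysis. Report mean assessment age by arm at each visit, which would also show whether timing differed.

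The cost is a few lines in the analysis plan and one derived variable, from the expected date of birth and the assessment date. No new measurement is needed. The small downside is reliance on an approximately linear age effect within the visit window, which the residual analysis already planned can check.
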